##### Patient outcomes

We are examining four primary patient outcomes. Patient outcomes are: (1) *Changes in quantity and frequency of substance use*. We measure this using the Timeline Follow-Back (TFLB), a validated instrument that uses a calendar to facilitate recall of substance use over the past 30 days [75]. (2) *Consequences of substance use*. To assess consequences, we use the Shortened Inventory of Problems Alcohol and Drugs (SIP-AD), a validated instrument that assesses consequences related to substance use in the past 90 days [76]. (3) *Functioning*. We assess overall health functioning with the SF12 version 2, four-week recall [77]. We use the Patient Health Questionnaire-9 (PHQ-9) [78] to assess depressive symptoms and the generalized anxiety disorder (GAD) [79] to assess symptoms of anxiety. (4) *Satisfaction with SUD care*. We use an adapted standardized patient satisfaction survey [80] to assess patient satisfaction with SUD services at the clinic.

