##### Analysis plan

Our quantitative analysis of provider survey items and administrative data related to service system outcomes will consist of pre-post, one-way repeated measures ANOVA comparisons of survey responses between pre- and all post-intervention periods. To analyze patient-level outcomes, we use an intent-to-treat approach. We will first conduct a bivariate analysis to estimate the uncontrolled association between being in the ICC group and outcome. In addition, even though our design randomly assigns patients, we will assess any possible imbalance in covariates between ICC and SAU groups including age, gender, race/ethnicity, and education that affect the impact of the ICC intervention on the outcomes. In cases where observed imbalances are attributable to sample attrition, we will correct for potential bias due to attrition at follow-up using response weights. In addition, characteristics related to an outcome at a conservative significance level of α = 0.2 will be considered covariates in a multivariate analysis for reduction of bias if imbalanced or for efficiency gains. For the multivariate analyses, we will infer about the impact of ICC on an outcome by fitting hierarchical models using SAS Proc Mixed, R LME4, and Winbugs. These models take into account the multi-level structure of the data: two repeated measures over time (baseline and 6 months) nested within patient and patients nested within clinics. Sensitivity analyses will be conducted testing model functional forms, the covariates to be used, and the impact of influential outliers in the analyses results. For outcomes assessed only at month 6 (e.g., treatment satisfaction), we will use cross-sectional analyses (such as linear and logistic regression) to estimate the effect of ICC relative to SAU. This study was designed to estimate sufficient effect sizes that can be detected with a power of at least 80% when comparing the outcomes of patients randomly assigned to the two conditions in an end-status analysis at month 6 for a 5% significance level. For continuous outcomes, the study will be able to detect effect sizes of about 0.30–0.32 standard deviations. These are the kind of effects that can be expected for an intervention like ICC [42]. For dichotomous outcomes, we will be able to detect a difference of 13–14 percentage points under the assumption that the SAU group has a 15% rate of receiving the outcome.

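### Four co-equal primary patient outcomes are paired with power that fits one 5% test: either the family-wise error rises to about 13–19%, or power under a four-way split is about 62%

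*Protocol article*

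**What the plan says.** Under Service delivery intervention, Patient outcomes, the protocol article says "We are examining four primary patient outcomes". It lists them without an order:

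1. Substance use, worded as "Changes in quantity and frequency of substance use" and measured by the Timeline Follow-Back.
2. Consequences of use, measured by the SIP-AD.
3. Functioning, measured by three instruments: the SF-12 ("We assess overall health functioning with the SF12 version 2, four-week recall"), the PHQ-9 for depressive symptoms, and the GAD "to assess symptoms of anxiety".
4. Satisfaction, using an adapted survey "to assess patient satisfaction with SUD services at the clinic".

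That is six instruments, or seven measures if quantity and frequency of use are scored separately.

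The Analysis plan under the same intervention gives power of at least 80% for a comparison of the two arms "in an end-status analysis at month 6 for a 5% significance level". The detectable effects are about 0.30–0.32 SD for continuous outcomes, and 13–14 percentage points from an assumed 15% usual-care rate for dichotomous outcomes. They are given generically and are not tied to a named outcome. Study design gives a total of 400 patients. The article states no rule for success across the four outcomes.

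**The concern.** Calling four outcomes primary says that each can carry the trial's main conclusion. The power statement is built as if there were one such outcome. The type I error or the power must give way, depending on how the four are combined, and the article does not say which.

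If the error gives way, a positive primary result has no known error rate. If the power gives way, the published detectable effects are too favourable for the family they are said to serve. The contents of the family add to the problem: the functioning domain holds three instruments and the substance-use domain names two quantities, so even the number of primary tests is not fixed.

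**Working it through.** **Inputs.** From the article: 400 patients, two arms, 80% power, 5% level, effects of 0.30–0.32 SD, 13–14 points from 15%, four primary outcomes. Assumed because not stated: two-sided tests, 1:1 allocation, normal approximation, and the correlation between outcomes (shown as a range).

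**Step 1: reproduce the stated figure.** Patients per arm for one test: n = 2(z₁₋α/₂ + z₀.₈)² / d², with z₀.₉₇₅ = 1.960 and z₀.₈ = 0.842.

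- d = 0.30: n = 2 × 2.802² / 0.09 = 174.4, so 175 per arm (350 analysed, 12.5% loss from 400).
- d = 0.32: n = 2 × 2.802² / 0.1024 = 153.3, so 154 per arm (308 analysed, 23% loss).
- Dichotomous, from 15%: 13 points needs 156 per arm and 14 points needs 137 per arm (171 and 151 with continuity correction).

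The published figures fit a single unadjusted 5% test with plausible attrition. With no loss at all, 200 per arm would detect 0.28 SD, so the 0.30–0.32 SD range is accounted for by attrition and leaves no allowance for four primaries.

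**Step 2: any one of four counts, each at 5%.** With no true effects and independent outcomes, the chance of at least one false positive is 1 − 0.95⁴ = 18.5%. Simulation of equally correlated test statistics (1,000,000 draws) gives:

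| Tests | r = 0 | r = 0.3 | r = 0.5 | r = 0.7 |
|---|---|---|---|---|
| 4 outcomes | 18.5% | 17.4% | 15.6% | 13.0% |
| 7 measures | 30.2% | 27.2% | 23.0% | 17.9% |

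The r = 0 column is exact (1 − 0.95ᵏ). The seven-measure row applies only if quantity and frequency are scored separately and every measure is tested as primary.

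**Step 3: alpha split across four (0.0125 each).** Power = Φ(d√(n/2) − z₁₋α/₂), with z₀.₉₉₃₇₅ = 2.498.

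- d = 0.30, n = 175: Φ(2.806 − 2.498) = Φ(0.309) = 62.1% (unadjusted: 80.1%).
- d = 0.32, n = 154: Φ(2.808 − 2.498) = Φ(0.310) = 62.2% (unadjusted: 80.2%).
- 13 points from 15%, n = 156: 61.8%.

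Effect detectable with 80% power: (2.498 + 0.842) × √(2/n), which is 0.357 SD at 175 per arm and 0.381 SD at 154 per arm. Keeping 80% power at the stated effects would need 248 per arm (0.30 SD) or 218 per arm (0.32 SD), both above the 200 per arm enrolled. If all 200 per arm were analysed, power would be 69% at 0.30 SD and 76% at 0.32 SD.

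**Step 4: all four must succeed.** The error rate then does not exceed 5%. If every true effect equals the stated detectable effect, joint power is 0.8⁴ = 41% for independent outcomes, and by simulation 56% at r = 0.5 and 62% at r = 0.7.

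**Step 5: one primary, or a fixed order.** The first test keeps 5% and 80%. The published figure holds for that test only.

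**The case against.** The strongest reply is that the article is a condensed account and the analysis plan is not shown. Multiplicity control, ordering and choice of score are commonly settled there, so their absence here is no fault. The 5% level appears only in the power statement. All of this stands, and three stronger readings that a reader might infer are therefore not supported:

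- *That any single significant outcome counts as a positive trial.* The article states no such rule. The hypotheses in the Background join the four outcomes with an and, which could equally be read as requiring all of them.
- *That the false positive rate is 16–30%.* That range joins four outcomes at correlation 0.5 to seven independent measures. It also needs unadjusted tests, an any-one rule and no true effects. The documents give no correlation, and seven is a count only if quantity and frequency are separated.
- *That satisfaction does not belong because few usual-care patients will have services to rate.* Study design has all patients screened as part of usual care, and the organizational readiness intervention introduces universal screening and brief intervention. The 15% usual-care rate is a generic planning value for dichotomous outcomes.

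Two further points limit the size. Holm or Hochberg would lose less power than an equal split. The planned models also use baseline and covariates: for illustration, with an assumed baseline-to-follow-up correlation of 0.5 and ANCOVA-type adjustment, the detectable effect is multiplied by √(1 − 0.5²) = 0.87, turning 0.36–0.38 into about 0.31–0.33 SD for outcomes measured at baseline.

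What the reply does not reach is the mismatch between two things that the article does state: four unranked primaries, and power that fits one test. An analysis plan could choose the testing rule, but it could not make the published power true for four co-equal primaries with a controlled error rate.

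**Conclusion.** The point holds in conditional form. If each of the four outcomes is tested at 5% and any one success counts, the family-wise error with no true effects is about 13–19% (assumed correlation 0.7 to 0), and higher if every instrument is tested. If the four are controlled by an equal split, power at the stated effects is about 62% and the detectable effect is about 0.36–0.38 SD in the stated month-6 comparison. If all four must succeed, the error is controlled but joint power is about 41–62% over the same correlations. Only a single primary or a fixed order keeps 80% power at 5%, and then only for the first test; the article's wording provides neither. These figures assume two-sided tests, 1:1 allocation and 154–175 analysed per arm. The correlations are assumptions, so the ranges are not bounds.

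**What to change.** Before any unblinded analysis, name one measure per domain, including one for functioning and one for substance use. Then choose one of two routes:

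- **(a) Keep four primaries.** Apply Holm or Hochberg across the four domains and restate the detectable effect as up to 0.36–0.38 SD, noting any gain expected from baseline adjustment.
- **(b) Rank them.** Name substance use as the single primary, or as the first in a fixed order, and state that 0.30–0.32 SD applies to that test only.

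If the analysis plan already contains such a rule, it is enough to state it alongside the power figure and make the two agree. The cost is wording: route (a) gives a somewhat less favourable detectable effect, and route (b) leaves fewer outcomes with primary status or has later tests depend on earlier ones. Neither needs more patients or data. Trial status puts the trial in month 11 of 18 planned months of enrolment and data collection, so the change could be made before analysis.

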##### Analysis plan

Our quantitative analysis of provider survey items and administrative data related to service system outcomes will consist of pre-post, one-way repeated measures ANOVA comparisons of survey responses between pre- and all post-intervention periods. To analyze patient-level outcomes, we use an intent-to-treat approach. We will first conduct a bivariate analysis to estimate the uncontrolled association between being in the ICC group and outcome. In addition, even though our design randomly assigns patients, we will assess any possible imbalance in covariates between ICC and SAU groups including age, gender, race/ethnicity, and education that affect the impact of the ICC intervention on the outcomes. In cases where observed imbalances are attributable to sample attrition, we will correct for potential bias due to attrition at follow-up using response weights. In addition, characteristics related to an outcome at a conservative significance level of α = 0.2 will be considered covariates in a multivariate analysis for reduction of bias if imbalanced or for efficiency gains. For the multivariate analyses, we will infer about the impact of ICC on an outcome by fitting hierarchical models using SAS Proc Mixed, R LME4, and Winbugs. These models take into account the multi-level structure of the data: two repeated measures over time (baseline and 6 months) nested within patient and patients nested within clinics. Sensitivity analyses will be conducted testing model functional forms, the covariates to be used, and the impact of influential outliers in the analyses results. For outcomes assessed only at month 6 (e.g., treatment satisfaction), we will use cross-sectional analyses (such as linear and logistic regression) to estimate the effect of ICC relative to SAU. This study was designed to estimate sufficient effect sizes that can be detected with a power of at least 80% when comparing the outcomes of patients randomly assigned to the two conditions in an end-status analysis at month 6 for a 5% significance level. For continuous outcomes, the study will be able to detect effect sizes of about 0.30–0.32 standard deviations. These are the kind of effects that can be expected for an intervention like ICC [42]. For dichotomous outcomes, we will be able to detect a difference of 13–14 percentage points under the assumption that the SAU group has a 15% rate of receiving the outcome.

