To address the need for change at two levels—organizational and service delivery system—to increase the intent and ability of primary care providers to identify and treat opioid and alcohol use disorders (OAUD), we designed a multi-level study to create and evaluate change at both levels. We call this study substance use motivation medication integrated treatment (SUMMIT) and focus on alcohol and opiate use disorders because of their relevance to the clinic population and availability of effective medications. At the organizational level, we test the effects of an organizational readiness intervention on the organization’s readiness to identify and treat individuals with opioid and alcohol use disorders. At the service delivery system level, we use Wagner’s Chronic Care Model [34] to reorganize and guide how care for OAUD is provided and supported; we call the service delivery intervention integrated collaborative care (ICC). Integrated, collaborative approaches have been successful in improving outcomes for patients experiencing a variety of different chronic illnesses, including diabetes [35], asthma [35], and depression [36]. ICC has improved implementation of evidence-based treatments and quality of care [37], lowered costs [38], improved patient outcomes [39-42], and is thought to be feasible for and sustainable in primary care clinics [43]. We test the effects of the organizational readiness intervention using a repeated measures pre-post design and the impact of the service delivery intervention on patient-level outcomes using a randomized controlled trial (RCT) to compare the service delivery intervention (ICC) with “service as usual” (SAU) on service system and patient outcomes. We hypothesize that provider (providers include administrators, medical and mental health providers, and other staff) readiness to implement the EBP and patient-centered SUD care will improve from the pre-organizational readiness intervention period (year 1) to the post-readiness intervention periods (years 2–5); that patients in the ICC condition will report more integrated, patient-centered evidence-based care for their opioid and/or alcohol use disorders, will be more likely to receive OAUD care, and will have lower overall health care utilization (e.g., emergency department and medical visits) than patients in the SAU condition; and that provider adoption of EBP will increase from year 2 to years 3 and 4 and that providers will still be delivering OAUD EBP a year after completion of the study in year 5. We also hypothesize that patients in the ICC condition will report less substance use, fewer SUD consequences, higher health and mental health functioning, and greater satisfaction with their SUD care 6 months after enrollment than SAU patients.

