### Study design

The study is designed to test the combined effect of both an organizational readiness intervention (which includes a 1-year organizational preparation period and an 8-month pilot of the ICC condition study) and a service delivery intervention (see Figure 2). We examine the effects of the interventions on organizational readiness, service system, and patient outcomes, all of which are believed to be important in understanding the uptake of new practices [58]. To test the unique effects of the organizational readiness intervention on provider outcomes, we use a pre-post-intervention design and measure these outcomes at the beginning of the study and then again at the end of year 1. At the end of year 1, we implement an eight-month pilot test of ICC. During the pilot test, providers gain experience with the protocols, and the protocols are iteratively adapted and refined based on provider feedback. Because we hypothesize that readiness outcomes may continue to improve as providers gain experience with ICC and the three treatments, we continue to measure organizational readiness outcomes annually at years 2–5. Thus, changes in outcomes between year 1 and years 2–5 reflect the combined effect of both the organizational readiness intervention and ICC on provider outcomes. To test the effects of the interventions on service system and patient-level outcomes, we are conducting an RCT to compare the effects of ICC with SAU. Service-system outcomes are patient-centered collaborative care, utilization of SUD treatment, patient utilization of health care services, provider adoption of EBP, and sustainability of EBP. Patient-level outcomes include substance use, consequences of use, physical and mental health functioning, and patient satisfaction with SUD care.

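### As written, record-based service use gets only a pre-post ANOVA with no arm contrast, although the hypotheses on that use compare ICC with SAU

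*Protocol article*

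**What the plan says.** All references are to the protocol article.

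- **Hypothesis (Background).** Compared with SAU patients, ICC patients "will be more likely to receive OAUD care, and will have lower overall health care utilization". This is a between-arm statement.
- **Purpose of the trial (Study design).** To test effects "on service system and patient-level outcomes, we are conducting an RCT to compare the effects of ICC with SAU".
- **Classification (Study design).** "Service-system outcomes are patient-centered collaborative care, utilization of SUD treatment, patient utilization of health care services" are listed first, followed by provider adoption and sustainability. A separate list follows: "Patient-level outcomes include substance use, consequences of use, physical and mental health functioning, and patient satisfaction with SUD care". Utilisation is not in the second list. The sections Service system measures and Patient outcomes keep the same split.
- **Analysis (Analysis plan, service delivery intervention).** "Our quantitative analysis of provider survey items and administrative data related to service system outcomes will consist of pre-post, one-way repeated measures ANOVA comparisons", which are then described as "comparisons of survey responses between pre- and all post-intervention periods". The next sentence brings in intent to treat, for patient-level outcomes.
- **Power (same section).** At least 80% power at the 5% level for a month-6 comparison of the two randomised conditions. The detectable effects are 0.30–0.32 SD for continuous outcomes and 13–14 percentage points for dichotomous ones, "under the assumption that the SAU group has a 15% rate of receiving the outcome".

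**The concern.** The plan names one method for administrative data on service-system outcomes, and that method cannot answer the question the trial asks of those data. A one-way repeated-measures ANOVA has time as its only factor. It tests whether the average moved between periods, not whether ICC patients moved differently from SAU patients.

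Receipt of treatment and use of health care are the outcomes closest to what ICC is meant to change. A before-after comparison of them gives up the protection of randomisation and takes in everything else that changed over the same period. The article documents two such changes: universal screening and brief intervention were introduced as part of the organisational readiness intervention (Interventions), and coverage was expanding rapidly in California (Discussion).

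If the text stays as it is, a central hypothesis has two very different candidate tests, and the choice between them could be made after the data are seen.

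**Working it through.** **Step 1. Reproduce the plan's power figures, to see which comparison they describe.**

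Inputs from the article: N = 400, 5% level, 80% power, SAU rate 15%. Assumed because not stated: 1:1 allocation, a two-sided test, and the attrition rate.

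Continuous outcomes: detectable difference = (1.960 + 0.842) × √(2/n), with n per arm.
- 400 analysed (n = 200): 2.802 × √(2/200) = 0.280 SD.
- 350 analysed (n = 175): 2.802 × √(2/175) = 0.300 SD.
- 308 analysed (n = 154): 2.802 × √(2/154) = 0.319 SD.

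Dichotomous outcomes: n per arm = [1.960 × √(2p̄(1−p̄)) + 0.842 × √(p₁(1−p₁) + p₂(1−p₂))]² / (p₂−p₁)², with p₁ = 0.15.
- 13 points (p₂ = 0.28): (1.139 + 0.483)² / 0.0169 = 155.6, so 312 in total, or 342 with continuity correction.
- 14 points (p₂ = 0.29): (1.148 + 0.486)² / 0.0196 = 136.3, so 274 in total, or 302 with continuity correction.

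About 302–350 analysed patients (roughly 12.5–25% attrition from 400) reproduces both stated ranges, using the continuity correction for proportions. The power statement is therefore sound, and it describes a between-arm test.

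**Step 2. Match each outcome to its data source and its named analysis** (sources from Service system measures).

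| Outcome | Source | Covered by the ANOVA sentence? | Hypothesis |
|---|---|---|---|
| SUD service use | Clinic records | Yes | ICC vs SAU |
| SUD service use | Patient self-report at follow-up | No | ICC vs SAU |
| Clinic health care visits | Clinic records only | Yes | ICC vs SAU |
| Emergency department visits | Patient self-report | No | ICC vs SAU |
| Provider adoption | Clinic records, provider survey | Yes | Change over years |

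Rows 1 and 3 are where the named method and the hypothesis part. Row 5 is where they agree: providers were not randomised, and adoption is hypothesised as a change from year 2 to years 3 and 4.

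**Step 3. What a pooled pre-post change can show.**

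Let s be a time trend common to both arms and t the ICC effect. The SAU arm changes by s and the ICC arm by s + t. With 1:1 allocation the pooled change is s + t/2, while the between-arm difference is t.

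| Trend s | ICC effect t | Pooled pre-post change | Between-arm difference |
|---|---|---|---|
| 0 | 13 points | 0 + 13/2 = 6.5 | 13 |
| 6.5 points | 0 | 6.5 + 0 = 6.5 | 0 |
| 13 points | 0 | 13 + 0 = 13 | 0 |

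The first two rows look identical to the ANOVA. The third, with no ICC effect at all, looks twice as large as a 13-point effect with no trend.

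**The case against.** The strongest reply is that the ANOVA sentence is loosely worded and that a by-arm analysis was always meant. Four points support this.

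- The sentence nearly repeats the analysis plan for the organisational readiness intervention and speaks of survey responses, which cannot describe encounter records. It could have been meant for provider surveys together with record-based adoption and sustainability, where a pre-post design is the only one available.
- Patient-level is used in two senses. The Background describes the RCT as testing ICC on patient-level outcomes and, in the same sentence, on service system and patient outcomes. The Conceptual framework says that service utilisation is measured at the patient level. On the wider sense, the intent-to-treat paragraph covers utilisation.
- The power statement is between-arm and speaks of receiving the outcome, which suits receipt of care.
- Outcomes assessed only at month 6 get linear or logistic regression of ICC against SAU. Self-reported service use at follow-up could fall there.

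These points stand as evidence of intent. They also defeat a stronger reading that a reader might infer, namely that the utilisation hypotheses are never tested by arm. The documents do not support that, because self-reported SUD services and emergency department visits are outside the ANOVA sentence.

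They do not supply a by-arm analysis for the administrative data. The sentence names those data for service-system outcomes without limiting them to adoption and sustainability, and Study design places utilisation among the service-system outcomes. Clinic health care visits have no other stated source, so the self-report argument cannot rescue them. Nor is this a detail that an article leaves to a fuller document: the article states a method, and the method does not fit the hypothesis.

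**Conclusion.** The point holds as a conflict between the stated analysis and the stated hypotheses. It is confined to administrative data on patient utilisation: record-based SUD service use and clinic health care visits. For these, the only named analysis has no ICC-versus-SAU contrast. A pooled change of 6.5 points would be equally consistent with a 13-point ICC effect and with none. That illustration assumes 1:1 allocation and arms pooled in the pre-post test; the trend values are illustrative.

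A reader might also infer that a pre-post rise in SUD treatment is almost certain even if ICC does nothing, since the clinic offered no such treatment before the study and patients currently in SUD treatment are excluded. The documents do not support a figure for this. They define no within-patient window before enrolment and give no pre-enrolment rate; pre and post in the article are study periods. The answer also depends heavily on the assumed rate. With 15% treated afterwards in both arms and 320–400 patients, a paired test rejects in 99–100% of simulated trials if 0–5% were treated before, but in only about half if 10% were.

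No stated power figure is wrong.

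**What to change.** 1. Restrict the pre-post ANOVA sentence to provider and clinic-level outcomes that have no randomised control: provider surveys (including the ACIC), adoption and sustainability.
2. State that patients' SUD-treatment use and health care use, from administrative records and from self-report, are compared by randomised arm under intent to treat over the 6 months after enrolment. Logistic regression for any treatment and a count model for visits would serve, adjusted for site and for pre-enrolment use where it is available.
3. Use patient-level in one sense throughout, so that it is clear which outcomes the intent-to-treat paragraph covers.

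The cost is analysis wording only. The encounter files are already being collected every 6 months, and the assignments are known. The sample size and the stated detectable effects stay as they are, since they already describe a by-arm test. The article reports month 11 of 18 planned months of enrolment and data collection, so at that stage the change could be made before the results were known.

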#### Service delivery intervention

We use Wagner’s Chronic Care Model (CCM) [35] as the theoretical basis for the service delivery intervention (ICC). The ICC intervention is comprised of five components that have been shown to result in improved patient outcomes; each component supports the delivery of the planned care for opioid and alcohol use disorders: (1) redesigning the delivery system to support the delivery of the EBP and establishing a care coordinator; (2) modifying clinical information systems to provide alerts to indicate that patients have problematic substance use and developing a patient registry used by the care coordinators to monitor and track patients; (3) providing expert consultation to therapists for complex cases; (4) offering patients self-management tools; and (5) identifying and establishing linkages with community resources. These components are thought to lead to productive patient-provider interactions, which, in turn, lead to improved service system and patient outcomes. The ICC components are described in greater detail in Additional file 1.

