##### Procedures

We use a combination of administrative records, patient interviews and staff surveys to evaluate service system and patient outcomes, as follows: 1) *Administrative records*. We collect three administrative files every 6 months—appointments (all appointments scheduled whether or not they were kept), encounters (including medical and therapy visit reasons and diagnoses), and medication orders. 2) *Patient interviews*. The patient interview contains an assessment of SUD diagnoses, substance use frequency and quantity, consequences related to use, and health and mental health functioning items. We administer patient interviews at baseline and 6 months after enrollment. 3) *Staff surveys*. Staff surveys are described above.

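### The month-6 attrition correction is triggered by observed covariate imbalance between arms, which can miss loss driven by engagement after randomisation

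*Protocol article*

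**What the plan says.** The rule is in the protocol article, Service delivery intervention, Analysis plan. The trial will assess "any possible imbalance in covariates between ICC and SAU groups including age, gender, race/ethnicity, and education". The next sentence sets the correction. Where an imbalance that is seen can be put down to attrition, "we will correct for potential bias due to attrition at follow-up using response weights". Observed covariate balance therefore decides whether attrition is corrected at all.

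The same paragraph states the principle, "To analyze patient-level outcomes, we use an intent-to-treat approach", and describes hierarchical models with "two repeated measures over time (baseline and 6 months) nested within patient and patients nested within clinics". Nothing measured between those two time points is assigned to the attrition correction. The listed sensitivity analyses cover functional form, covariate choice and outliers; none addresses missing data.

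Three other places bear on this:
- **Study design.** Follow-up is a single telephone interview at 6 months.
- **Service delivery intervention (under Interventions) and Background.** ICC includes "developing a patient registry used by the care coordinators to monitor and track patients", and its patients are hypothesised to be more likely to receive care for their opioid or alcohol use disorder.
- **Procedures.** Every 6 months the trial collects "appointments (all appointments scheduled whether or not they were kept), encounters (including medical and therapy visit reasons and diagnoses), and medication orders". These files do not depend on the interview. The Service system measures section uses them as outcomes; no section uses them for attrition.

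**The concern.** Covariate balance among respondents says little about the kind of loss this design invites. Suppose patients who drift away from care are harder to interview and also do worse. ICC is built to change how many patients drift away, and may change how closely drifting away is tied to non-response. Respondents in each arm then stop representing their arm, in different ways, yet age, gender, race/ethnicity and education can stay balanced because the selection works through something that happened after baseline. The rule would then trigger no weights, and the report could read as though attrition had been checked and found harmless.

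At stake are the outcomes that come from the 6-month interview: substance use, consequences of use, functioning and satisfaction. Utilisation measured from clinic records has no interview attrition and is not affected.

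**Working it through.** **1. The plan's own figure.** Inputs from the protocol: N = 400, power at least 80%, 5% significance, detectable effect 0.30-0.32 SD. Assumed: two-sided test, 1:1 allocation. Formula: n per arm = 2(1.960 + 0.842)²/d².
- d = 0.30: 174.4, so 175 per arm, or 87.5% of 200 (12.5% lost).
- d = 0.32: 153.3, so 154 per arm, or 77% of 200 (23% lost).
- With all 200 per arm the detectable effect is 2.802 × √(2/200) = 0.28 SD.

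The power statement is therefore true. Its range fits an unstated allowance of about 13-23% loss for the trial as a whole.

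**2. Closed form, engaged yes/no.** None of these inputs is in the protocol. Let p be the engaged share, r1 and r0 the response rates of engaged and disengaged patients, and g the effect of engagement on outcome in SD. Among respondents the engaged share is m = p·r1/(p·r1 + (1−p)·r0), so the arm mean shifts by g(m − p). The bias is the ICC shift minus the SAU shift; plus means the ICC benefit is overstated.
- *Link in ICC only* (p = 0.40, r1 = 0.95, r0 = 0.70; SAU response unrelated to engagement): m = 0.38/0.80 = 0.475. With g = 0.5 the bias is +0.5 × 0.075 = +0.037 SD.
- *Link in SAU only* (p = 0.15, same r1 and r0): m = 0.1425/0.7375 = 0.193. With g = 0.5 the bias is −0.5 × 0.043 = −0.022 SD.
- *Same link in both arms* (p = 0.29 or 0.40 in ICC and 0.15 in SAU, r1 = 0.95, r0 = 0.60-0.80, g = 0.3-0.8): +0.004 to +0.036 SD.

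**3. Does the trigger notice, and do baseline variables help?** A simulation of 400,000 patients used the ICC-only case with SAU response flat at 80%:

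| Quantity | ICC − SAU (SD) |
|---|---|
| True effect | 0.128 |
| Respondents only | 0.165 |
| Adjusted for baseline outcome and a baseline covariate | 0.167 |
| Weighted by arm and engagement | 0.128 |
| Baseline covariate difference among respondents | about 0.000 |

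Follow-up was 79.9% in both arms, so equal response rates gave no warning either.

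**4. Continuous engagement.** Assumed: ICC raises engagement by 0.5 SD, outcome coefficient g = 0.3-0.5, logistic response, 80% follow-up in both arms. Bias = g × (respondents' excess mean engagement in ICC minus that in SAU).

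| Log-odds of response per SD of engagement, SAU / ICC | Bias (SD) |
|---|---|
| 1 / 1 or 1.5 / 1.5 | 0.00 |
| 1 / 0 | −0.05 to −0.09 |
| 1.5 / 0 | −0.07 to −0.11 |
| 0 / 1 | +0.05 to +0.09 |
| 0 / 1.5 | +0.07 to +0.11 |

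Swapping the arm with the stronger link flips the sign and leaves the size unchanged.

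**The case against.** The strongest reply is that the article never lists the variables in the weight model. The four demographics belong to the balance check, the list is open, and a condensed article may leave weight content to a fuller plan. That stands. A reader might infer that the weights use baseline demographics only; the text does not say so. What the article does fix is the condition for weighting, and the point rests on that.

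A reader might also infer that the ICC effect will be understated and power lost, because disengaged SAU patients are the ones who disappear. The documents do not support a direction. Nothing says in which arm engagement is more closely tied to response, and the last table in the working shows both signs.

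Nor can the 77% and 87% retention figures be read as SAU and ICC rates. They are the two ends of a range back-calculated from one power statement, for both arms together.

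Finally, the interview is by telephone, so response need not follow clinic attendance, and nothing ties the care coordinators to interview contact. That is fair: the mechanism is plausible, not shown. With the same link and equal follow-up in both arms, the continuous model gives no bias. But the planned rule cannot tell the harmless case from the harmful one.

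**Conclusion.** The concern holds as a weakness in a stated rule. Observed covariate balance is the wrong test for whether interview loss matters, because loss through engagement after randomisation can bias the month-6 contrast without disturbing that balance.

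The size is unknown, since no attrition rate is given. Under the assumed inputs the bias runs from about 0 to roughly 0.1 SD of either sign, against a design effect of 0.30-0.32 SD. It requires engagement to relate to both response and outcome, and the arms to differ in engagement, in the response link or in overall response. That ICC changes engagement is the trial's hypothesis. That the clinic files cover all randomised patients is inferred from the Procedures and Service system measures sections, and extends only to care at this clinic. This should be changed, with medium confidence.

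**What to change.** Drop the imbalance condition. For every month-6 interview outcome, apply response weights, or multiple imputation by arm, regardless of observed covariate balance. Fit the response model separately in ICC and SAU, using:
- baseline outcome or severity (substance use, SIP-AD score), diagnosis and site;
- clinic-record data from baseline to month 6: kept and missed appointments, encounters and medication orders.

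Use the record variables only in the response or imputation model, never as covariates in the outcome model, so that the ICC estimate remains intent-to-treat. Report response by arm.

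The cost is analysis-plan wording and linkage of files already collected. Weights become somewhat more variable: in simulation the standard error rose by at most about 6%. Bias removal will be partial if the records measure engagement poorly (about half was removed when they carried substantial error) or if patients receive care elsewhere. The Trial status section puts the RCT at month 11 of 18, so the rule could still be settled before the arms are compared.
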